#### Secondary outcome measure

SAS: the Zung SAS is an anxiety measure designed by William WK Zung in 1971 to quantify the level of anxiety for patients experiencing anxiety-related symptoms [28]. The SAS test is self-administered, with each response using a 4-point scale, ranging from “none of the time” to “most of the time.” There are 20 questions with 15 increasing anxiety level questions and five decreasing anxiety questions. According to SAS standard scores, the respondents are divided into four categories: no symptoms of anxiety (< 50 points); mild anxiety (50–59 points); moderate anxiety (60–69 points); and severe anxiety (≥ 70 points). The scale has been widely used in China and its validity and reliability have been verified.Metabolic profile: TC, TG, HDL-C, and LDL-C.Body composition: weight and BMI.

#### Safety outcome measures

The safety assessment will be performed for the participants who have received VBE training more than once. The individuals’ vital signs and general physical status will be examined at every visit. The occurrence of adverse events (AE) will be checked at visits 3, 4, 5, 6, 7, and 8. The investigators should educate the individuals to report any AE that occurs after training. All AEs that occur after the start of this trial should be documented in the case report form, whether or not they are related to VBE. All AEs will be evaluated for causal relationships.

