## Methods

### Study design and setting

This is a 6-month, single-blind RCT that will be conducted in the First Affiliated Hospital of Soochow University. Written informed consent will be obtained from each individual by the researcher after the individual has received a sufficient explanation and period of time in which to make a thoughtful decision. All the patients will be randomized 1:1 into the VBE-based clinical trial monitoring group (n = 70) or the Routine follow-up group (n = 70). The VBE-based clinical trial monitoring group is given VBE training on the basis of conventional treatment and health education, while the control group received conventional health education and follow-up. The two groups will be followed up for 3 months (Step 1). Considering the ethics and the fairness of the resources, we refer to the step-wedge design [30] and give the control group the same VBE guidance and follow up for another 3 months (Step 2) (see the flow diagram in Fig. 2). The Cardiovascular Medicine Department of the First Affiliated Hospital of Soochow University is currently the largest cardiovascular disease diagnosis and treatment center in South Jiangsu Province, China. The department carried out the first PTCA surgery in China in 1983. It has 180 beds, including 20 fully equipped Coronary Care Unit (CCU) beds, four cardiac catheterization rooms with advanced equipment, as well as a cardiac supersonic room and cardiac function room, and 1500 m^2^ cardiovascular laboratory. Annually, an average of 100,000 outpatients, 5000 open-heart surgery candidates, and 400 emergency operations are treated in the department.

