Attention: The participants should breathe in and out of the nose during the whole process. The intensity of the exercise should not cause breath-holding or any physical discomfort. If discomfort occurs, participants may rest for a while and continue the exercise if no discomfort is present. For the first 3 days of the study, participants are asked to complete exercises in an outpatient classroom and the researchers will assess whether the exercises are correct or if they need to correct wrong breathing patterns.
4.Exercise log: each participant is given an exercise log and asked to record the number and time of exercise every day. These data can be used to assess intervention compliance.5.Network support: the research group will make self-breathing exercise material or video and transmit it to each participant through the network, so that participants could browse at any time.

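### The stated safety set requires more than one VBE session, so read literally it omits one-session patients and, in Step 1, every control

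*Protocol article*

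**What the plan says.** The only definition of a safety population in the protocol article is in Safety outcome measures: "The safety assessment will be performed for the participants who have received VBE training more than once".

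The recording rule in the same section is wider: "All AEs that occur after the start of this trial should be documented in the case report form". It covers events judged unrelated to the exercises as well as related ones. The section adds that all AEs are to be evaluated for causal relationship. On timing it says "The occurrence of adverse events (AE) will be checked at visits 3, 4, 5, 6, 7, and 8". Table 1 shows the same AE checks (weeks 1, 2, 3, 4, 8 and 12) and does not split them by arm. The instruction to patients, however, is tied to exposure: "The investigators should educate the individuals to report any AE that occurs after training".

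On exposure, Study design and setting says that in Step 1 "the control group received conventional health education and follow-up". Controls receive VBE guidance only in Step 2, after the 3-month comparison, and the Control group section repeats this.

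**The concern.** A safety set exists to count everyone who met the intervention, and people who could not tolerate it matter most. A threshold of more than one session removes a patient whose only session went badly. The protocol allows for discomfort during the exercise (Intervention group: "If discomfort occurs, participants may rest for a while and continue the exercise if no discomfort is present"), so first-session intolerance is foreseeable.

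The second effect does not depend on how many patients stop early. A set defined by VBE exposure has no controls in it while the randomised comparison runs. Patients with coronary disease will have some AEs over 12 weeks whatever they are assigned to. Without a concurrent unexposed rate in the safety assessment, attribution to VBE rests on case-by-case causality judgement, although the design supplies a randomised comparator.

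**Working it through.** The plan states no AE rate and no size for the safety set, so there is no figure to reproduce. The check sets the definition against exposure in each arm.

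**Inputs**
- Arm size: 70 and 70 (Randomization).
- Entry to the safety set: more than one VBE training, literally at least 2 sessions (Safety outcome measures).
- VBE sessions in Step 1: controls 0; VBE arm from the start, with the first 3 days in the outpatient classroom (Study design and setting; Intervention group).
- Scheduled follow-up contact: VBE arm weekly in month 1 and then monthly; controls monthly (Intervention group; Control group).

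**Step 1. Who is in the set during the randomised comparison**

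| Group | Sessions in Step 1 | In the set as written | If 'at least once' was meant |
|---|---|---|---|
| VBE, continuing | 2 or more | yes | yes |
| VBE, stopped after one session | 1 | no | yes |
| Control | 0 | no | no |

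The set holds at most 70 of 140 patients (50%) and 0 of 70 controls. Controls enter only once exposed in Step 2, so they never supply an unexposed rate.

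**Step 2. Direction of the effect in the VBE arm**

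Let *k* patients stop after one session because of an AE, and let *m* of the remaining patients have an AE.

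- All exposed: (*m* + *k*)/70
- More than one session: *m*/(70 − *k*)

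The second is never larger than the first: *m*·70 ≤ (*m* + *k*)(70 − *k*) reduces to *m* + *k* ≤ 70 for *k* > 0, which always holds. This covers patients who stop because of an AE. Dropping one-session patients who had none would raise the rate slightly; for example, 3/70 = 4.3% becomes 3/67 = 4.5%.

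**Step 3. Illustration with assumed counts, *m* = 3**

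| *k* | All exposed | More than one session |
|---|---|---|
| 1 | 4/70 = 5.7% | 3/69 = 4.3% |
| 2 | 5/70 = 7.1% | 3/68 = 4.4% |
| 3 | 6/70 = 8.6% | 3/67 = 4.5% |
| 5 | 8/70 = 11.4% | 3/65 = 4.6% |

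The rate under the rule as written barely moves as first-session stopping rises. For an event seen only at first sessions, 3/70 = 4.3% (exact 95% CI 0.9% to 12.0%) would appear in the assessed set as 0/67 (0 to 5.4%).

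**Step 4. Recorded set against assessed set**

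Recording, causal evaluation and the Table 1 checks are not limited by arm or by number of sessions. Withdrawal criteria also keeps withdrawn patients in follow-up for outcomes. Only the sentence defining the safety assessment is limited.

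**The case against.** The strongest reply is that little or no information is lost. All AEs go into the case report form and are evaluated for cause, whatever the arm. A reader might infer that first-session events are hidden, that controls contribute nothing, or that the randomised comparison of AEs is irretrievable. The documents support none of these: the events should be on record, and a control rate could be built from them. Nor is there a contradiction. Recording AEs for everyone and summarising safety in a subset can both be done; what is missing is any statement of how the wider record is used.

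Second, the wording may be a slip for at least once. Even read literally, it drops only someone who stops for good after one session, in a programme of more than 30 minutes a day that can be split into batches of at least 10 minutes. This is fair, and it makes the first consequence less certain. It does not touch the second, because controls have no sessions in Step 1.

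Third, AE tables by arm are usually left to an analysis plan, which is not shown. Their absence is not the criticism here. The criticism is of a set that the article does fix, and that leaves no controls to tabulate in Step 1.

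Fourth, the counts above are invented. That stands: they show direction and mechanism, not an expected size.

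**Conclusion.** The point holds as a defect in the stated safety set. The exclusion of all 70 controls from the Step 1 safety assessment follows from the text under either reading of the phrase. The exclusion of one-session patients follows only from the literal reading; where such patients stopped because of an AE, it lowers the VBE rate by an amount that cannot be estimated, since the documents give neither an AE rate nor an early-stopping rate. The assessed set is narrower than the recorded set, and the article does not reconcile them. The safety conclusion is affected; the primary HRV and RPP comparisons are not.

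**What to change.** Replace the sentence with a Step 1 safety set of all randomised patients, counting in the VBE arm everyone with at least one session, including a partial one, together with all controls. Summarise AEs by arm from the checks scheduled in Table 1. Report controls' AEs after they start VBE in Step 2 separately, as uncontrolled exposure data. Word the patients' reporting instruction so that it also applies to people who have had no training.

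The cost is mostly wording, with one real downside. Scheduled follow-up contact in month 1 is weekly for VBE and monthly for controls, so AEs may be picked up more often in the VBE arm. Either base the between-arm comparison on the time points common to both arms, or confirm that the Table 1 visits apply to both arms and state any remaining difference in ascertainment. RPP, a primary outcome, is measured at Visits 4, 7 and 8, which suggests that controls attend at least those visits, but the article should say so. Asking controls at every VBE time point would need extra contacts if they now receive only the monthly calls.

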#### Protocol supplementary

The researchers will collect the exercise logs of the patients after 2 weeks of exercise for the purpose of calculating exercise compliance. The rate of compliance will be calculated as: compliance (%) = [continuous regular exerciser/total intervention group] * 100. Clinical trials will be continued only if compliance is ≥ 70%.

### Data management and quality control of data

Both the electronic medical record and web-based electronic database will be used to manage individual participant data. To protect confidentiality, the files are stored in a secure and locked place and manner. Quality control of the data will be handled at two different levels: the investigators will be required to ensure the accuracy of the data as the first level of control when they input the records in electronic medical record. The second level will include data monitoring and validation that will be carried out by two full-time graduate students who will not be involved in the intervention or data collection. The database will be locked under the orders of the Principal Investigator. All the data will be double-inputted into the computer using Epidata3.0 software. After checking and proofreading, SPSS statistical software (SPSS Inc., Chicago, IL, USA) will be used for data analysis. Nobody can have access to the database without authorization from the Principal Investigator.

### Statistical analysis

The Kolmogorov–Smirnov test and p-p diagram analysis will be used to test the normal distribution of continuous variables. Continuous variables will be presented by mean ± SD if they are normally distributed. Mann–Whitney U test will be used and expressed by median with interquartile range if they are not normally distributed. Chi-square or Fisher’s exact tests will be used for comparison of dichotomous data. Both per-protocol (PP) and ITT analyses will be used to determine the robustness of the evidence. An independent statistics expert will perform the statistical analysis in a blind manner. All statistical analyses of the data will be performed by using SPSS software version 21.0 (SPSS Inc., Chicago, IL, USA). A multivariate analysis will be performed to identify the factors associated with outcome indicators. Statistical significance is obtained with a *P* value < 0.05.

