## Background

Stable coronary artery disease (SCAD) is one of the most common types of coronary artery disease. It is characterized by chronic delay and high recurrence. Several studies [1–3] have demonstrated that pathological changes of coronary heart disease can lead to dysfunction of the cardiac autonomic nervous system, which is manifested as hyperactivity of sympathetic nerve and decreased excitability of vagus nerve. Thayer et al. [4] concluded that autonomic nervous dysfunction leads to cardiac dysfunction and cardiovascular disease. Patients are also at an increased risk of complications such as malignant arrhythmia (ventricular flutter, ventricular fibrillation, etc.), increased heart rate, increased systolic blood pressure, and increased rate-pressure product (RPP), which is highly correlated with myocardial oxygen consumption and indirectly reflects myocardial blood supply and oxygen consumption [5], and is earlier than the change of electrocardiography (ECG). RPP is the product of heart rate and systolic blood pressure and has been used as a non-invasive indicator to assess the level of myocardial oxygen consumption since the 1970s. The basis of the common pathophysiology of the risk complications such as angina pectoris and acute coronary events is myocardial ischemia and hypoxia. RPP is closely related to myocardial oxygen consumption (*R* = 0.90) [6], which is not only used to formulate the amount of exercise prescribed, but also the basis for evaluating the symptoms and exercise ability of patients with cardiovascular disease. To some extent, it reflects the tolerance and safety of certain rehabilitation methods of cardiovascular patients. As a consequence, it is of utmost importance to no longer neglect the stability of autonomic nervous function during rehabilitation of SCAD. Heart rate variability (HRV) is recognized as a new non-invasive quantitative evaluation method of autonomic nervous system function developed in recent years [7]. HRV refers to the small difference between cardiac cycles, which reflects the sympathetic and vagus nervous systems regulating the balance state of the cardiovascular system [8]. It was shown to be related to subtle time changes and patterns of each cardiac cycle, while the average heart rate can only appear normal or abnormal. Shen et al. [9] analyzed the results of 24-h dynamic electrocardiogram of 156 patients with coronary heart disease and found that HRV decreased, ejection fraction decreased, and the incidence of cardiovascular events increased.

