#### Exclusion criteria

Patients will be excluded from the study if:
Revascularization has been carried out or conducted in follow-upCombined arrhythmia shows on an ECGAny self-reported respiratory disorderSevere liver and kidney diseasesDiagnosed with hypothyroidism or currently taking thyroid medicationsDiagnosed with moderate or below anemia (hemoglobin [Hb] level < 9 g/dL)With any mental disorders (for example, major depressive disorder, anxiety disorder, substance use, etc.) in the past 12 monthsPregnancy and/or practicing yoga/meditation/relaxation/mindfulness on a regular basisOther reasons determined by the investigators that make participation in the clinical trial inappropriate

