#### Withdrawal criteria

Participants who meet the criteria summarized below are withdrawn from the study. The individuals who are withdrawn after randomization will be followed up for outcomes. Reasons for withdrawal will be documented in follow-up records and data will be analyzed using the intention-to-treat (ITT) principle [34]:
Failed to exercise for 2 weeks in a rowFailed to have three consecutive telephone connections during the follow-up periodPatients who quit for various reasons

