#### Intervention group

After enrollment, the intervention group was given the following measures on the basis of receiving the routine health education. Each patient in the intervention group will be assigned a health management document and have a follow-up timetable.
Development and distribution of manuals: the Chinese Biomedical Literature Database (CBM) will be searched using the Chinese search terms “health management,” “diet,” “exercise,” “heart rate,” and “blood pressure” and the Cochrane Library, JBI, and Medline will be searched using the corresponding English search terms. After two rounds of expert consultation, the health education manual for patients with SCAD will be constructed and distributed to each patient in the intervention group upon discharge.One-to-one telephone follow-up or home visit: the patient will be followed up after discharge. Follow-up time is 3 months for a total of 12 weeks (once a week in the first month and once a month after that until 3 months). Two follow-up methods will be adopted: telephone and home visit. The telephone follow-ups last about 5–10 min each. Holding time could be extended if there is any problem consultation. Home visits will be scheduled with patients in advance and will last about 30–60 min each. During the follow-up, we will address the patient’s doubts and evaluate the effectiveness of the intervention.VBE guidance: before VBE, patients should rest for 5 min and then do it in a well-ventilated room with appropriate temperature. The researchers help patients take comfortable positions (supine, repose, and standing are all acceptable, sitting is recommended), straighten their head and back, and relax their whole body. The researchers instruct patients to extend the duration of exhalation and inhalation, and to minimize the breathing rate to 6 breaths/min. Participants practice silently counting from 1001 to 1004 on the inhale phase and 1001–1006 on the exhale phase to control the breathing rhythm and slow down the frequency. Participants are also encouraged to use abdominal breathing (a bulge in the abdomen when inhaling and a depression when exhaling) to deepen breathing depth and reduce breathing rate. Practice time: the total time per day is more than 30 min [25], which can be delivered in batches, but for at least 10 min at a time and at least five times a week [12].

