#### Control group

Routine education: on the first day after enrollment, researchers explain relevant knowledge of SCAD to patients, including risk factors, diet, weight control, physical exercise, blood pressure, lipid management, etc.Telephone follow-up: once per month for 3 months, each call lasting about 5–10 min, receiving telephone counseling from patients.Post-intervention: the control group will be given the same intervention measures 3 months later, and the effects of the control group will be compared before and after the intervention.

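### The exclusion criteria reach revascularisation during follow-up, which read literally conflicts with the ITT commitment, and no rule says how such patients are analysed

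*Protocol article*

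**What the plan says.** Three parts of the protocol article bear on this.

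- **Exclusion criteria.** The list opens with "Patients will be excluded from the study if". Its first item is revascularisation, either already performed or performed during follow-up.
- **Withdrawal criteria.** "The individuals who are withdrawn after randomization will be followed up for outcomes", and "data will be analyzed using the intention-to-treat (ITT) principle". Three reasons for withdrawal are listed: two successive weeks without exercise, three consecutive failed telephone contacts, and patients quitting for any of various reasons. Revascularisation is not among them.
- **Statistical analysis.** "Both per-protocol (PP) and ITT analyses will be used to determine the robustness of the evidence". Neither analysis set is defined further.

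The primary outcomes are the changes in HRV and RPP. Table 1 schedules HRV at screening and visit 8 (week 12) only, and RPP at visits 1, 4, 7 and 8.

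**The concern.** An eligibility criterion should rest on facts known before randomisation. The second half of the revascularisation item, taken at its word, can be met only later. It therefore acts as a rule for removing randomised patients, placed outside the section that promises follow-up and ITT analysis for those who leave.

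The event is unlikely to be unrelated to the outcomes. The Background says that the shared basis of complications such as "angina pectoris and acute coronary events is myocardial ischemia and hypoxia", and it uses RPP as a marker of myocardial oxygen consumption. The Discussion says that ischaemia raises sympathetic activity and lowers HRV. Selecting on this event could therefore select on HRV and RPP.

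Two things are at stake. The first is which patients make up the ITT set. The second is whether the data for a true ITT analysis will exist. HRV has one scheduled post-baseline measurement, so a patient who leaves before visit 8 has no HRV change score, and no later analysis plan can recover it.

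**Working it through.** **The passages side by side**

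1. Exclusion criteria: revascularisation in follow-up leads to exclusion from the study.
2. Withdrawal criteria: patients withdrawn after randomisation are followed and analysed by ITT, but the listed reasons do not include this event.
3. Statistical analysis: ITT and PP are both promised, with no statement of which set holds these patients.

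Statement 1 taken literally and the ITT promise in 2 and 3 cannot both be applied to a randomised patient who is later revascularised. They can be reconciled only if exclusion in follow-up is treated as a withdrawal, and the article does not say so.

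**Size, by assumption only**

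The article gives no revascularisation rate and no outcome difference for these patients, so there is no plan figure to reproduce. The planned effect size of 0.447 (Sample size section) serves only as a yardstick.

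Let p be the share of an arm that is removed, and let D be the number of SDs by which those patients' mean outcome is worse than the whole arm's mean. Set the arm mean to 0. The remaining mean m satisfies (1 − p) × m + p × (−D) = 0, so m = p × D / (1 − p). The shift in the VBE-minus-control difference, with higher meaning better, is

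pV × D / (1 − pV) − pC × D / (1 − pC).

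| Control | VBE | Removed of 70 (control, VBE) | D | Shift (SD) | Share of 0.447 |
|---|---|---|---|---|---|
| 5% | 5% | 3.5, 3.5 | 0.5 or 1 | 0 | 0% |
| 5% | 2% | 3.5, 1.4 | 0.5 | 0.010 − 0.026 = −0.016 | 4% |
| 5% | 2% | 3.5, 1.4 | 1 | 0.020 − 0.053 = −0.032 | 7% |
| 10% | 3% | 7.0, 2.1 | 0.5 | 0.015 − 0.056 = −0.040 | 9% |
| 10% | 3% | 7.0, 2.1 | 1 | 0.031 − 0.111 = −0.080 | 18% |

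The negative sign arises only because the table assumes more removals among controls and D worse than average. Swapping the arms reverses it, and so does assuming that the removed patients do better. Equal rates do not guarantee zero if D differs by arm: at 5% in both arms, with D of 1 in one and 0.5 in the other, the shift is 0.053 − 0.026, about 0.026 SD in size.

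**The case against.** The strongest reply is that the article never says these patients leave the ITT set. The exclusion list governs participation, and the analysis rule sits under Withdrawal criteria. Someone taken out after randomisation is naturally a withdrawn patient, to be followed and analysed under that rule, and the last withdrawal reason is broad. This reading is available, and it is why the point is an unreconciled conflict. A reader might infer that the plan does analyse a reduced set and call it ITT, but the text does not establish that. What remains is that the event is listed under exclusion and not under withdrawal, and that quitting describes a patient's choice, not a rule imposed by the protocol.

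A second reply is that the wording may be awkward English for past or planned revascularisation, an ordinary screening criterion. That is possible, and if so the correction simply makes it plain.

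A third is that analysis sets are commonly defined in a fuller document. That would excuse silence. It does not excuse a stated exclusion rule that pulls against a stated analysis principle.

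Some stronger inferences should be resisted.

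- **A large or directional bias.** A 10-point gap, with removed patients 1 to 1.5 SD worse than those remaining, would give 0.10 × 1 = 0.10 to 0.10 × 1.5 = 0.15 SD, or 22% to 34% of 0.447. That needs 7 more patients of 70 removed from one arm within the 3-month comparison, in patients enrolled as stable. Visit 8 values would also be measured after the procedure, and the documents do not say which way HRV and RPP would then move.
- **More referrals from closer contact in the VBE arm.** VBE contacts run "once a week in the first month and once a month after that until 3 months", which is 4 + 2 = 6, while the control section has "Telephone follow-up: once per month for 3 months", which is 3. Table 1, however, shows visits at weeks 1, 2, 3, 4, 8 and 12 with vital signs and adverse event checks, without separating arms. Nothing links contact frequency to revascularisation.
- **Losses on top of the 20% dropout allowance.** The Sample size section does not itemise that allowance, so these patients may already be within it.

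**Conclusion.** The point holds as a conflict in the text. An exclusion rule that reaches a post-randomisation event stands against an ITT commitment, and the withdrawal rule that could reconcile them does not name the event. The consequence is conditional: the ITT set departs from the randomised set only if these patients are dropped or their visit 8 data are not collected.

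The size and direction of any bias cannot be found from the documents. Under the assumed gaps of 3 to 7 points and deficits of 0.5 to 1 SD it is roughly 0.02 to 0.08 SD, about 4% to 18% of the planned effect. It is zero when rates and outcome differences are equal across arms, and it is probably small over 3 months. The documents do not show that the randomised comparison is lost for HRV and RPP. The correction is still worth making because it is cheap and because uncollected outcomes cannot be recovered.

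**What to change.** - In the Exclusion criteria, limit the revascularisation item to procedures before randomisation.
- In the Withdrawal criteria, state that patients revascularised after randomisation stay in outcome follow-up, have visit 8 HRV and RPP collected, are analysed in their allocated arm under ITT, and are counted and reported by arm.
- In the Statistical analysis section, confine any omission of these patients to the PP or a sensitivity analysis.

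The cost is a few sentences and the effort of obtaining visit 8 measurements from these patients. The change concerns data collection and analysis, not care. The downside is that post-procedure values add some noise to the ITT analysis; the PP or sensitivity analysis can show the result without them. Trial status reports 16 of 140 patients recruited, so at that point the clarification could still have covered most of the sample.
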